**Figure 2 F2:**
[figure not shown]
**Remuneration Flow Diagram**. Flow diagram of study design and group allocation for remuneration substudy, including payments schedule for pharmacists. (q4 weeks = every 4 weeks; q3 months = every 3 months).

### Intervention

The intervention (Table 2) is based upon the recommendations of CHEP [18,19]. Pharmacists assess patients with regards to BP control and cardiovascular risk reduction. The pharmacist also reviews the patient's current hypertensive therapy regimen and decides upon the options for improvement of BP control and implementation of these strategies. Pharmacists encourage adherence to antihypertensives. A fax is sent to the patient's primary care physician outlining the strategies discussed and implemented at the baseline visit. In some cases, depending on the proximity to the physicians, pharmacists may discuss the changes in person. Patients are followed at four-week intervals until achievement of target BP for two consecutive visits and, thereafter, at three-month intervals until study completion. To support pharmacists, there is "hotline" access to hypertension experts via email or telephone. Participating pharmacists submit questions that are either answered by a member of the study coordinating center or are forwarded to one of the hypertension experts on the steering committee.

**Table 2 T2:** Components of enhanced pharmacist care

Intervention Component	Detailed Description
Blood pressure control	• Review current blood pressure control and treatment goals • Modify antihypertensive regimen as required (increase dose, additional antihypertensives, change administration schedule) • Order blood work as required with medication changes

Cardiovascular risk reduction	• Assessment of concomitant conditions and appropriate treatment (*e.g*., diabetes management, dyslipidemia, obesity)

Education	• Wallet card to record blood pressure readings, patient-related information from the Canadian Hypertension Education Program [17] • Lifestyle parameters for implementation (weight loss, salt intake, smoking cessation, alcohol intake, physical activity)

Collaboration with physicians	• Meeting with local physicians prior to study start to discuss collaboration and address any concerns, provide physicians with a communication package • Fax/letter regarding patient's enrollment in the study as well as notification regarding prescriptions

Adherence	• Simplified regimens, home blood pressure monitoring, and/or identification of adherence barriers

Close follow-up	• Every four weeks until patient reaches target for two consecutive visits, then every three months

### Control group

Patients randomized to the control group receive usual care (which is actually more than typical "usual care" in these settings): a wallet card for BP readings and a pamphlet on BP. Patients are seen at 12 weeks for interim BP measurement only. Both groups of patients are seen at 24 weeks for final BP measurements. If the pharmacist has a concern regarding control patients' BP during the study, they are to make recommendations to the physician and refer patient to physician, as appropriate. Usual-care patients will be offered intervention care at the end of the follow-up; as such, prescribing by the pharmacist for control patients can occur after 24 weeks.

### Outcomes

The primary outcome is the change in SBP between baseline and 24 weeks in the enhanced-care versus usual-care arms. All BP measurements are made using BpTRU^® ^(BpTRU Medical Devices, Coquitlam, British Colombia, Canada), an approved and validated measuring instrument, as per CHEP [18]. Secondary outcomes include the number of patients at their BP target at 24 weeks, the number of new antihypertensive medication starts, the number of antihypertensive dosage changes (dose increases or decreases), the number of antihypertensive medication changes, and the number of new prescriptions for aspirin and cholesterol medications. Pharmacists will be asked to participate in end-of-study focus groups to determine their opinions on the different remuneration models.

### Setting

Pharmacists and pharmacies are selected based on their current practice model, size, and location of the community (population of < 20,000 and located more than one-hour driving distance from Edmonton and Calgary) and willingness to apply for additional prescribing authorization.

Currently we have 15 sites involved in the study, with two sites that have multiple pharmacists participating. The majority of sites are community pharmacies, but sites also include pharmacists in primary care networks and hospital-based pharmacists who provide some outpatient services. All study data are collected in the pharmacy and faxed to the study office using unique patient identifiers to conceal the identity of the patients.

### Prescribing authorization

Pharmacists participating in the study must be authorized to prescribe as defined by the Health Professions Act in Alberta [14]. In order to do this, pharmacists must have at least two years of patient-care experience and have successfully completed an application process. The study team assists pharmacists in implementing documentation systems and accruing the information required to complete their application. To that end, pharmacists attend educational seminars with local hypertension experts that help fulfill the requirement for demonstrating continued education in the area of interest. In addition, pharmacists recruit a run-in of at least three patients and conduct all elements of the intervention except the prescribing portion (patient identification, assessment, education, recommendations to physician). This run-in can serve as the basis for pharmacists to ensure that they routinely perform all the key activities that are required for additional prescribing authorization

### Sample size and statistical analysis

Based on a two-sample, two-sided *t*-test, a sample size of 162 will provide 80% power to detect a minimally important clinical difference (MCID) of 8 mm Hg between intervention and usual-care groups, with a projected standard deviation of 18 in each group [12]. In the comparison of different payment models within the intervention arm, an alpha of 0.10 was used for a total of 224 patients to detect a 6 mm Hg MCID between the fee-for-visit group and the payment-for-performance group.

Assuming a drop-out or loss to follow-up rate of 10%, the sample size has been increased to 250 in the intervention group (125 in fee for service and 125 in payment for performance) and 90 in the usual-care group, for a total sample size of 340.

All analyses will be intention to treat. A comparison of baseline characteristics will be performed using *t*-tests or nonparametric Wilcoxon for continuous variables and chi-squared test for categorical variables. In order to account for any imbalance in baseline characteristics, the test for differences in change in SBP between intervention and usual-care groups will be adjusted for using multiple regression models (or analysis of covariance models). The problem of missing values will be checked for nonrandomness, and appropriate imputation methods will be applied when needed. All analyses will be carried out using SAS 9.1.3 (SAS Institute, Cary, NC, USA).

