**Figure 1 F1:**
[figure not shown]
**Study Flow Diagram**. Flow diagram of randomization and follow-up of patients based on group assignment. Patients in enhanced care are followed up more closely until target blood pressure is reached. Patients randomized to usual care only have two follow-up visits. (HBPM = home blood pressure monitoring, q4 weeks = every 4 weeks, q3 months = every 3 months).

The primary objective is to evaluate the effect of enhanced pharmacist care on SBP in patients with poorly controlled hypertension in the rural setting. Secondary objectives include the number of patients at their BP target at 24 weeks, the number of new antihypertensive medication starts, the number of antihypertensive dosage changes (increases and decreases in dose), the number of antihypertensive medication changes, and the number of new prescriptions for aspirin and cholesterol medications.

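### Imputation of missing 24-week SBP should not depend on a check for nonrandomness, because a clean check cannot justify leaving patients out

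*Protocol article*

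**What the plan says.** All of the relevant planning text is in the protocol article, mostly under Sample size and statistical analysis.

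- Analysis set: "All analyses will be intention to treat".
- Missing data: "The problem of missing values will be checked for nonrandomness, and appropriate imputation methods will be applied when needed".
- Model: the comparison of change in SBP "will be adjusted for using multiple regression models (or analysis of covariance models").
- Expected loss: "Assuming a drop-out or loss to follow-up rate of 10" per cent, giving 250 enhanced-care and 90 usual-care patients, 340 in total.

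Under Outcomes, "The primary outcome is the change in SBP between baseline and 24 weeks in the enhanced-care versus usual-care arms", so a patient without a 24-week reading has no primary outcome value.

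Interim SBP is collected in both arms. The Intervention section has enhanced-care patients seen four-weekly until they are at target on two consecutive visits, then three-monthly. The Figure 1 legend says "Patients randomized to usual care only have two follow-up visits", which the Control group section places at 12 and 24 weeks.

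**The concern.** The missing-data sentence couples a look at the data with a decision about whether to impute. That is a poor rule for two reasons.

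First, the check cannot answer the question put to it. Observed data can show that missingness is related to baseline SBP, arm or interim SBP. They cannot show that it is unrelated to the 24-week SBP that was not recorded. Finding nothing is not evidence that loss is harmless.

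Second, even for patterns that are visible in principle, a check on roughly 34 missing patients is weak.

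If the check is clean and imputation is judged unnecessary, the regression runs on completers. Randomized patients then drop out of the primary comparison on the strength of an uninformative test. If loss in one arm is related to how SBP was progressing, the estimated treatment effect is shifted, although readings already collected could have corrected for it.

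**Working it through.** **1. The plan's own figures.** The plan states that "a sample size of 162 will provide 80% power to detect a minimally important clinical difference (MCID) of 8 mm Hg", "with a projected standard deviation of 18 in each group". The alpha for this test is not given; I assume two-sided 0.05. The exact two-sample t calculation with effect 8/18 gives 80.44 per arm, so 81 per arm and 162 in total (power 0.803). Dividing by 1 − 0.10 gives 81/0.9 = 90, the planned usual-care arm; 112/0.9 = 124.4, rounded up to 125 per payment group, gives 250. The figures reproduce. Expected loss is 0.10 × 340 = 34 patients (25 enhanced care, 9 usual care), leaving 306 (225 and 81).

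**2. Power of a baseline check.** Two-sample t-test of baseline SBP, missing versus observed, two-sided 0.05:

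| Comparison | True difference | Power |
|---|---|---|
| 34 v 306 | 0.2 SD | 0.20 |
| 34 v 306 | 0.3 SD | 0.38 |
| 34 v 306 | 0.4 SD | 0.60 |
| 9 v 81 (usual care only) | 0.3 SD | 0.135 |

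**3. What such a check cannot see.** I simulated 4,000 trials per scenario with 250/90 patients, no true effect, SD 18 and about 10% loss. The check compared baseline SBP of missing and observed patients, and loss by arm. It flagged 8.9% of trials when loss was completely random. It flagged 8.8% when enhanced-care loss depended on the unseen 24-week change (drawn independently of baseline; gap about 17.6 mm Hg between missing and observed patients). In the second case completers were biased by 1.7 mm Hg and type I error was 0.126. This shows that the check is uninformative. It does not measure what the fix would gain, because imputation under missing at random leaves that bias in place.

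**4. Bias that the fix would remove.** For an enhanced-care arm with missing share d, and dropouts whose 24-week SBP averages D mm Hg above completers with the same baseline, the completer estimate is off by d × D if usual-care loss is random. The documents do not give D, so I simulated it.

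- Assumptions: SBP at 12 and 24 weeks, given baseline, each with SD 18 and correlation 0.5 to 0.7; log-odds of enhanced-care loss rising by 0.5 to 1.0 per SD of 12-week SBP; 10% loss in each arm, random in usual care; 12-week SBP available for everyone; 3,000 trials per setting.
- Moderate dependence (0.5 per SD, correlation 0.5): D about 4.4, bias 0.10 × 4.4 = 0.44 mm Hg.
- Strong dependence (1.0 per SD, correlation 0.7): D about 11, bias about 0.10 × 11 = 1.1 mm Hg.
- In every setting, imputing within arm from baseline and 12-week SBP brought the bias to within 0.05 mm Hg of zero.
- A check on baseline SBP alone stayed clean in about 95% of trials. Adding 12-week SBP, it still stayed clean in about half of trials under moderate dependence, but in only about 7% under strong dependence.

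**5. Effect on the test.** With 225/81 completers, SE = 18 × √(1/225 + 1/81) = 2.33. A bias of 1.0 mm Hg moves two-sided type I error from 0.05 to about 0.07.

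**The case against.** The strongest reply is that the sentence does not say that imputation happens only if the check is positive. The clauses are joined by a plain conjunction, and the closing condition could mean no more than that imputation applies wherever values are missing. Alongside an intention-to-treat commitment, that reading is possible. It stands to this extent: a reader might infer that the protocol prescribes a completers-only analysis and so contradicts itself, but the text says neither. It leaves that analysis open. A check placed directly before a conditional is still most naturally read as a trigger, and nothing in the article closes off that reading.

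Several stronger inferences should also be resisted.

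- That interim readings are discarded, that the method will be chosen after seeing unblinded data, or that no sensitivity analysis exists. The article is a condensed account and the analysis plan is not shown; that plan may settle all three.
- That the shift could reach a quarter of the target difference. That needs 20% loss, twice the planned rate, and enhanced-care dropouts 10 mm Hg worse than comparable completers: 0.20 × 10 = 2 mm Hg. It is also outcome-dependent bias, which imputation under missing at random would not remove, so it cannot be charged to the conditional rule.
- That arm-dependent loss is likely. Visit frequency differs by arm, but enhanced-care visits thin out once target is met, usual-care patients are offered the intervention after follow-up, and the plan assumes one loss rate throughout. Loss that differs only by arm does not bias a completers-only analysis of covariance.

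What the reply does not answer is that a clean check is no reason to omit imputation.

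**Conclusion.** The point holds in a limited form. The article states a conditional rule, and the condition cannot do its job: a clean check neither excludes dependence on the unseen 24-week SBP nor, at the planned loss, reliably detects dependence on what was observed. The rule can therefore lead to a completers-only primary analysis that fits poorly with intention to treat.

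The likely harm is modest, about 0.4 to 1.1 mm Hg or 5% to 14% of the 8 mm Hg target (0.4/8 to 1.1/8). This rests on 10% loss, on enhanced-care loss that depends on 12-week SBP, and on the assumed correlations and slopes. At the upper end, a check that included 12-week SBP would usually raise a flag, so silent bias is more probable towards the lower end. The bias is zero if loss depends only on arm and modelled baseline values. The rule should be changed because a better one costs little, not because the trial's conclusion is in clear danger.

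**What to change.** Remove the check as a trigger; patterns of missingness can still be described. State that all randomized patients enter the primary comparison, with missing 24-week SBP handled by one prespecified method valid under missing at random, whatever the pattern looks like. Examples are multiple imputation within arm, or a mixed model, using baseline SBP and the interim SBP already collected.

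As a recommended addition, include a delta-adjusted sensitivity analysis that shifts imputed enhanced-care values upward in steps and reports where the conclusion changes. No method that assumes missing at random removes bias from loss that depends on the unseen outcome.

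The cost is a change of wording and modest programming. No new data and no change in sample size are needed. If the analysis plan already fixes such a method unconditionally, it is enough to bring the article's wording into line with it.

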### Research Ethics

Ethics approval for the study has been obtained from the University of Alberta Health Research Ethics Board.

### Substudies

#### Examining the effect of different remuneration models for pharmacists

Current remuneration for community pharmacists in Alberta is based on a per-prescription fee. However, with the advancement of pharmacy services to a patient-centered care model, research into other payment models is a priority. A recent review of remuneration systems for pharmacy services demonstrated a wide variety of models in place, with little analysis of outcomes and sustainability [21].

The objective of this substudy is to evaluate the clinical effect of two pharmacist remuneration models: a payment-for-performance model versus a fee-for-visit model.

Patients randomized into the intervention arm of the study are further randomized in a 1:1 ratio into either payment-for-performance or fee-for-visit remuneration models for the pharmacist. For those patients randomized into the fee-for-visit remuneration model, the pharmacist providing care receives a payment of $150 CDN for the first visit (expected to last approximately 60 minutes) and $75 per visit thereafter (expected to last approximately 20 minutes, plus 10 minutes for documentation), up to a maximum of six visits (Figure 2). For patients randomized into the payment-for-performance remuneration model, the pharmacist providing care receives $150 for the initial visit and $75 for each additional visit as outlined above, and also receives a bonus of $125 if the patient reaches 50% of their target (*i.e*., 50% of the change from baseline needed to reach target) and/or $250 if the patient reaches their target BP for two consecutive visits.

The primary outcome for this substudy is a comparison of SBP reduction achieved between patients in the payment-for-performance remuneration group versus the fee-for-visit remuneration group at six-months follow-up.

#### Understanding effects of enhanced pharmacist care on patient's hypertension knowledge

There is a potential lack of knowledge translation from clinicians to patients. Recently, a number of studies have been conducted assessing the knowledge of hypertensive patients regarding their condition. These studies have shown that most patients have little if any knowledge regarding their hypertension or the potential long-term sequelae of hypertension [22-26]. One study that specifically focused on patient attitudes towards hypertension found that only 35% of hypertensive patients felt that high BP was a serious health concern, and over 35% also felt that high BP was unavoidable [25]. Patient knowledge of hypertension, its causes and symptoms, and the seriousness of having uncontrolled BP must be improved upon.

The objective of this substudy is to evaluate the effect of enhanced pharmacist care on patient knowledge. Two surveys are administered to all patients enrolled in the study. One survey is to be completed at the time of enrollment, while the other is an exit survey. Survey questions are designed to determine patients' level of knowledge regarding hypertension and blood pressure [25], as well as patients' level of understanding and experience with pharmacy interventions [27,28].

We plan to compare hypertension knowledge at baseline and at follow-up between the control and intervention patients. Other outcomes include a comparison of the knowledge levels of patients in the control and intervention groups regarding pharmacists' contribution to patient care and any differences in knowledge between those patients randomized to the payment-for- performance versus fee-for-visit intervention models. These analyses will only be completed for those patients who complete the intervention.

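### The knowledge substudy keeps only patients who complete the intervention, contrary to the intention-to-treat rule and with no meaning for usual care

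*Protocol article*

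**What the plan says.** The section on sample size and statistical analysis sets a general rule with no exception: "All analyses will be intention to treat". It then says that missing values will be checked for nonrandomness and that "appropriate imputation methods will be applied when needed". That section covers both the main arm comparison and the payment-model comparison.

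The hypertension knowledge substudy states its aim as follows: "The objective of this substudy is to evaluate the effect of enhanced pharmacist care on patient knowledge". On data collection it says: "Two surveys are administered to all patients enrolled in the study", and "One survey is to be completed at the time of enrollment, while the other is an exit survey". The main comparison is given as: "We plan to compare hypertension knowledge at baseline and at follow-up between the control and intervention patients". Further comparisons concern knowledge of the pharmacist's contribution to care, and the two randomised payment groups. The section then closes with: "These analyses will only be completed for those patients who complete the intervention".

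The section on the control group gives usual-care patients a wallet card and a pamphlet. It adds: "Patients are seen at 12 weeks for interim BP measurement only". They have a final measurement at 24 weeks and are offered the intervention only once follow-up has ended.

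**The concern.** The closing sentence fixes an analysis set, so it is not detail left to an analysis plan. It has three faults.

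- It contradicts the general intention-to-treat rule.
- It selects patients on an event that follows randomisation. Enhanced care includes education and close follow-up, so staying with it is plausibly related to engagement and so to knowledge.
- It cannot be applied as written to the control arm.

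The substudy's aim is the effect of enhanced care on knowledge. A set of completers does not in general estimate that effect. The payment-model comparison is exposed in the same way if completion differs between the two payment groups. That is possible, because only one of them carries a bonus tied to blood pressure results. Since the sentence has several readings, the analysis set could also be chosen after the data have been seen.

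**Working it through.** **Stated figures.** The knowledge substudy gives no sample size, power or effect size of its own. The trial's figures reproduce.

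- A difference of 8 mm Hg, SD 18, 80% power and a two-sided alpha of 0.05 (assumed, as it is not stated) need 160.9 patients by the t-test, so 81 per arm or 162 in total.
- A difference of 6 mm Hg at alpha 0.10 needs 224.
- Allowing for 10% loss, 224 / 0.9 = 249 (stated as 250) and 81 / 0.9 = 90.

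The 10% is therefore applied in both arms, and the article describes it as drop-out or loss to follow-up.

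**What the filter could mean.** Taking 10% as an illustrative share excluded, 250 x 0.9 = 225 and 90 x 0.9 = 81.

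| Reading | Enhanced care | Usual care |
|---|---|---|
| Literal, in both arms | 225 | 0, as no control receives the intervention before 24 weeks |
| Filter on enhanced care only | 225 | 90, before any missing surveys |
| Completing follow-up, in both arms | 225 | 81 |

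The enhanced-care side is not clear either. Under the intervention section, visit frequency depends on reaching target blood pressure at two consecutive visits, so no fixed number of visits marks completion.

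**Bias formula.** Let p be the share excluded in an arm, and d the mean score of completers minus that of non-completers, in SD units. The mean of the whole arm is (1 - p) x completer mean + p x non-completer mean. The completer mean therefore exceeds the arm mean by p x d.

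**Filter in the enhanced arm only.** The arm contrast shifts by p x d. No value of d stands in the documents, and p for non-completion of the intervention does not either. Both are assumptions.

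| p | d = 0.25 SD | d = 0.5 SD | d = 1 SD |
|---|---|---|---|
| 10% | 0.025 | 0.05 | 0.10 |
| 20% | 0.05 | 0.10 | 0.20 |

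To see what 0.05 SD does to a nominal 5% two-sided test with no true effect, take 225 against 90 patients and unit SD. The standard error is sqrt(1/225 + 1/90) = 0.125, the shift is 0.05 / 0.125 = 0.40 standard errors, and the test rejects 6.9% of the time. With p = 20% and d = 0.5 (200 against 90), it rejects 12.4% of the time.

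**Filter in both arms.** The shift is p1 x d1 - p0 x d0, where 1 is enhanced care and 0 is usual care. With 10% and 0.5 SD in each arm it is 0.05 - 0.05 = 0. It differs from zero only if the loss or the gap differs between arms.

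**The case against.** The strongest reply is that the authors probably meant patients who finish the study period and so have an exit survey. A literal reading would remove every control and make the planned comparison impossible, and the surveys are meant for all enrolled patients. On that reading the filter acts in both arms and may cause little or no bias. This stands. A reader might infer that the sentence sets the most engaged enhanced-care patients against unselected controls and so must favour enhanced care. The documents do not support that: one-arm selection is only one reading, and the claim that non-completers know less is plausible but undocumented.

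It also stands that the protocol's 10% is not a rate of non-completing the intervention, so it cannot serve as evidence that 0.05 SD will occur. Nor does removing the sentence recover patients lost to follow-up. They have no exit survey under either rule and remain a missing-data problem. What is recovered is the group seen at the end without having completed the intervention. Its size is not given and may be small.

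None of this removes the conflict. On every reading the analysis is confined to completers, while the statistical section promises intention to treat for all analyses.

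**Conclusion.** The concern holds as a contradiction and as a badly fixed analysis set. The restriction conflicts with the stated intention-to-treat rule, conditions on an event after randomisation, and is undefined for usual care.

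The size of any bias is conditional. It is p x d if the filter falls on enhanced care alone, which is 0.05 SD at the assumed 10% and 0.5 SD and modest in its effect on the false-positive rate. It is zero if the filter falls on both arms with equal loss and equal gap. The same reasoning applies between the two payment groups.

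The substudy is secondary and has no stated power. The primary systolic blood pressure analysis and the sample size of 340 are not affected.

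**What to change.** Replace the closing sentence of the knowledge substudy with a rule that:

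- analyses all randomised patients in the group to which they were assigned, for both the arm comparison and the payment-model comparison;
- uses every exit survey obtained, whether or not the intervention visits were completed;
- handles missing exit surveys under the missing-data provision already in the statistical section;
- keeps any completer analysis as a labelled supplement, with completion defined in the same way in both arms.

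The cost is low, since both surveys are already planned for all enrolled patients. The article does not say when the exit survey is given. If it is now given only to patients who complete the intervention visits, offering it to the others is a small addition to data collection. Otherwise the downside is a possibly slightly diluted estimate and a little more analysis work. The article reports one-third of the sample recruited, so at that stage the wording could still be settled before analysis.
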